## Data analysis

Investigators and their supporting statistics departments will conduct data analysis. Site differences will be analysed. Analyses will provide important descriptive data, such as prevalence rates and lifestyle data, proportion treated to target for CVD, diabetes and diabetic retinopathy risk factors and predictors of diabetic retinopathy and CVD outcomes. Analysis of covariance (ANCOVA) will be used to compare differences between groups. To assess confounding, covariates will include age, gender, and established and emerging risk factors for CVD, diabetes and diabetic retinopathy, as appropriate. Non-parametric statistics will be used when assumptions for parametric methods are violated. All tests will be conducted using an alpha level of 0.05 and 95% confidence intervals will be reported.

Complete case analysis and, where reasonable, multiple imputation will be employed for the management of missing data. Missing data may occur due to drop-out, missed assessments or item non-response. With knowledge of the missing data mechanism, all available information can be used. One approach will be to use the multilevel model, a full-likelihood method that allows for a response to be missing at random, where missingness depends only on observed data and not on unobserved data. Another strategy involves imputing missing values by multiple imputation procedures.

The proposed economic evaluation aims to include pre- and post-study resource utilization costs for both the costs and consequences and a cost consequence analysis (CCA). Standard unit costs i.e. Australian Medicare Benefits Schedule will be applied to the resource-use data. Costs will be presented in total and disaggregated forms, such as those from different sectors — the health sector, patients and government.

Of the recruitment target of 600 Indigenous Australians with diabetes, to date 576 participants have been recruited and undergone retinal imaging for diabetic retinopathy screening.

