**Methods:**

Using a pre-post intervention design, 600 Indigenous Australians with type 2 diabetes will be recruited from three primary-care health-services in the Northern Territory. Diabetes status will be based on clinical records. There will be four technological interventions: 1. Baseline retinal imaging [as a real-time patient education/engagement tool and telehealth screening strategy]. 2. A lifestyle survey tool administered at ≈ 6-months. 3. At ≈ 6— and 18-months, an electronic cardiovascular disease and diabetes decision-support tool based on current guidelines in the Standard Treatment Manual of the Central Australian Rural Practitioner’s Association to generate clinical recommendations. 4. Mobile tablet technology developed to enhance participant engagement in self-management. Data will include: Pre-intervention clinical and encounter-history data, baseline retinopathy status, decision-support and survey data/opportunistic mobile tablet encounter data. The primary outcome is increased participant adherence to clinical appointments, a marker of engagement and self-management. A cost-benefit analysis will be performed.

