Telehealth facilitation of service delivery and disease management has the potential to improve health outcomes for people with diabetes and to improve the quality of service delivery in the primary care setting. Currently, there are inadequate data to support the widespread clinical uptake of telehealth technologies. Therefore, the ‘Telehealth Eye and Associated Medical Services Network’ [TEAMSnet] study aims to address the knowledge gaps in three areas — telehealth facilitation of 1. diabetic retinopathy screening 2. evidence-based diabetes and CVD management (via decision support and survey tools) and 3. patient self-management strategies.

This paper presents the protocol for the TEAMSnet study. This technology-based pre-post intervention study aims to describe the baseline characteristics of the participants with diabetes and clinical workflows in partner health service and to investigate the impact of telehealth facilitation in the management of CVD, diabetes and diabetic retinopathy. We hypothesise that telehealth facilitation of diabetes management will lead to improvements in patient engagement [attendance rates and survey participation] and clinical outcomes, such as blood pressure and metabolic control.

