## Methods/Design

### Study design

This is a pre-post study of technology-facilitated management of diabetes, CVD, and diabetic retinopathy. We plan to enrol 600 adults (age ≥18 years) with clinically-diagnosed diabetes from three remote Northern Territory Aboriginal-controlled health services — Central Australian Aboriginal Congress [CAAC] in Alice Springs, Miwatj Health Aboriginal Corporation [Miwatj] that incorporates the four clinics at Nhulunbuy, Galiwin’ku/Elcho Island, Yirrkala, Gunyangara/Ski Beach in East Arnhem Land and Wurli-Wurlinjang Health Service [Wurli] in Katherine. Recruitment and intervention are anticipated to occur over a 3-year period. Participants will receive retinal imaging, diabetic retinopathy screening, including diabetes education, at baseline, followed by lifestyle assessment six months later, including self-management support. An electronic CVD and diabetes decision support tool that includes an Indigenous-specific CVD risk calculator, based on best-practice as generally defined by guidelines in the current Standard Treatment Manual of the Central Australian Rural Practitioner’s Association [CARPA], will be developed in conjunction with a clinical working group and used to generate a clinical recommendations report to assist clinicians with evidence-based management of CVD, diabetes and diabetic retinopathy approximately 6–18 months after baseline. Mobile tablet technology based on clinical input and feedback will be developed to support clinical staff and participants with engagement in diabetes management and self-management, respectively.

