#### Pre-study data

Site partners will collaborate to audit the Communicare EHR for each participant in order to obtain the required pre-study data i.e. the data that correspond with post-study data relating to CVD, diabetes or diabetic retinopathy risk and outcomes and each participant’s use of health services, such as eye-care consultations and hospitalizations.

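### The stated comparative method, ANCOVA between groups, does not estimate the within-participant pre-to-post change in appointment adherence that is the primary outcome

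*Protocol article*

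**What the plan says.** **Design.** Under Study design the article states: "This is a pre-post study of technology-facilitated management of diabetes, CVD, and diabetic retinopathy". No control arm and no allocation are described. The planned sequence is given for participants as a whole: "Participants will receive retinal imaging, diabetic retinopathy screening, including diabetes education, at baseline, followed by lifestyle assessment six months later".

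**Data.** Under Pre-study data, each participant's electronic health record is to be audited for "the data that correspond with post-study data relating to CVD, diabetes or diabetic retinopathy risk and outcomes". Each person therefore contributes a before and an after value.

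**Primary outcome.** The abstract states: "The primary outcome is increased participant adherence to clinical appointments, a marker of engagement and self-management". The hypothesis in the Background speaks of attendance rates. The scale (binary, count or rate) is not fixed.

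**Analysis.** The Data analysis section states: "Analysis of covariance (ANCOVA) will be used to compare differences between groups". On the adjustment of these comparisons, the section goes on to specify that "covariates will include age, gender, and established and emerging risk factors for CVD, diabetes and diabetic retinopathy, as appropriate". Pre-study attendance is not named as a covariate. As a fallback, "Non-parametric statistics will be used when assumptions for parametric methods are violated". The section also plans an analysis of site differences, without naming a method for it, and mentions a multilevel model as one of two ways to deal with missing responses.

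**The concern.** The question the study asks is whether the same people attend more reliably after the intervention than before. The comparative method it names contrasts different people with one another. The article defines no groups apart from the three services, so a reader who follows the text would compare sites or subgroups and would obtain no estimate of the pre-to-post change. A reader who takes the two periods as the groups would have a test of the right contrast, but with a standard error that ignores the pairing.

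At stake is which analysis carries the primary conclusion. The article reports that 576 of the 600 participants are already recruited, so the model for the primary outcome should be fixed in writing before outcome data are examined.

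**Working it through.** The plan gives no figure for this point. The Sample Size figures (minimum 490, target 600) cannot be reproduced from the stated inputs, because no base rate is given, and nothing below depends on reproducing them.

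**Step 1. The target.** Let Y₀ and Y₁ be a participant's attendance before and after. The primary outcome calls for δ = mean of (Y₁ − Y₀) over participants.

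**Step 2. Groups read as sites or subgroups.** Suppose attendance rises by the same δ in groups j and k.
- Post-study means: (μⱼ + δ) − (μₖ + δ) = μⱼ − μₖ.
- Changes: δ − δ = 0.

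Either way δ cancels, so the contrast says nothing about whether attendance rose. The usual ANCOVA of a post value adjusted for its baseline needs a comparator arm, and pre-study attendance is not in the covariate list anyway. The listed covariates suit a comparison between people. A fixed trait such as gender cannot confound a comparison of a person with himself or herself.

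**Step 3. Groups read as the pre and post periods.** Take equal variance σ² in both periods, n participants and within-person correlation ρ.
- Variance of the difference, pairing ignored: 2σ²/n.
- Variance of the difference, pairing respected: 2σ²(1 − ρ)/n.
- Ratio of variances: 1/(1 − ρ). Ratio of standard errors: 1/√(1 − ρ).

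| Assumed ρ | Variance ratio | SE ratio | Actual size of a nominal two-sided 5% test |
|---|---|---|---|
| 0.3 | 1/0.7 = 1.43 | 1.20 | 2Φ(−1.96 × 1.195) ≈ 0.019 |
| 0.5 | 1/0.5 = 2.00 | 1.41 | 2Φ(−1.96 × 1.414) ≈ 0.006 |

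The document gives no ρ, so these values are assumptions. For positive ρ the error makes intervals too wide and tests too cautious.

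**Step 4. Consequence of that reading at the planned effect.** Inputs from Sample Size are a 15% differential (taken as 15 points), 25% attrition and 600 enrolled, so 600 × 0.75 = 450 completers. Assume a binary outcome with a rate near 50%.
- SE with pairing ignored: √(2 × 0.25/450) = 0.033.
- z = 0.15/0.033 ≈ 4.5.
- Power ≈ Φ(4.5 − 1.96) = Φ(2.54), above 99%.

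**Step 5. Is sample size the issue?** For a paired binary outcome, the McNemar approximation is n = (1.96√p_d + 0.84√(p_d − d²))²/d², with d = 0.15 and discordant proportion p_d, for 80% power and two-sided 0.05. It gives 50 pairs at p_d = 0.15, 173 at 0.5 and 347 at the extreme of 1.0. The article states no p_d, but all these values lie below 490. The difficulty is the method named, not the number of participants.

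**The case against.** The strongest reply is that the ANCOVA sentence is never labelled the primary analysis. It stands close to the statement that site differences will be analysed and follows a list of descriptive and predictor analyses, for which ANCOVA can be proper. The article is a condensed account, and a missing primary model could simply sit in an analysis plan that is not shown. The multilevel model is of the right class, since a full-likelihood model copes with missing responses by being the analysis model. The unspecified non-parametric tests might be paired ones, such as McNemar or Wilcoxon signed-rank.

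Much of this stands, and it rules out several stronger readings that a reader might infer:
- **That ANCOVA is the only method mentioned, so the trial cannot test its primary hypothesis.** The multilevel model and possibly paired non-parametric tests are also there. What is missing is any link from them to the pre-post attendance comparison.
- **That every participant receives every component, so no groups could exist.** The abstract describes tablet encounters as opportunistic, and the objectives foresee evaluating the technologies' cost-efficacy individually as well as together. Varying uptake may form subgroups, but it does not create a comparison arm.
- **That ANCOVA fails because attendance cannot be normal.** The outcome scale is not fixed. For a per-person rate in a sample of this size the approximation may be tolerable.
- **That the fallback necessarily loses covariate adjustment.** The article does not say which non-parametric methods are meant.

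The mismatch itself survives. The article does more than stay silent: it states a between-groups method for a design without comparison groups, and it ties no other method to the primary outcome.

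**Conclusion.** The point holds as a mismatch between the stated comparative method and the design. Read as sites or subgroups, the ANCOVA carries no information on the within-participant change in appointment adherence. Read as periods, it overstates the standard error by 1/√(1 − ρ), or 1.20 to 1.41 at ρ of 0.3 to 0.5. Those figures rest on an assumed correlation, equal variances and one of two possible readings.

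A reader might infer that the primary result would be invalid or the effect missed. The documents do not support that. With positive ρ the error is conservative and does not add false positives, and at a 15-point change with 450 completers and a rate near 50% the power stays above 99% even with the pairing ignored. The text should be corrected before analysis so that the primary test is unambiguous. This is a correction to the analysis wording and does not call for a change in design or sample size.

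**What to change.** State in the analysis plan that the primary analysis is a within-participant model of attendance with a pre/post period term, participant as the clustering unit and site as a fixed effect, and that the period effect is reported with its 95% confidence interval.

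- **Outcome form.** Use mixed-effects or GEE logistic regression if attendance is binary, or for appointments attended out of those scheduled if scheduled appointments are recorded in the health record. The article mentions encounter history, eye-care consultations and hospitalizations but does not say that scheduled or missed appointments are captured, so this must be confirmed first. Otherwise use a count model with a log person-time offset.
- **Site by period.** Examine this interaction only as a secondary check, so that the main period effect keeps one meaning across sites.
- **Blood pressure and metabolic measures.** Use the multilevel model already named, in linear form, with the same period, participant and site structure.
- **ANCOVA.** Keep it for between-site or subgroup comparisons, and say so in the sentence that names it.

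The cost is analysis-plan wording and slightly more modelling work.

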## Discussion

It is well-known that a significant number of individuals with diabetes fail to adhere to screening recommendations and/or adequately self-manage diabetes-related risk factors and consequences. Furthermore, primary care service delivery for diabetes and its complications is challenging, even in well-resourced environments with a large proportion of patients at low risk of diabetes complications and related conditions, such as depression. Importantly, the disease burden of diabetes in Australia is greatest amongst Indigenous Australians, particularly in remote settings.

Telehealth facilitation of service delivery and diabetes management has potential benefits. To date, there are insufficient data to answer the question ‘Can telehealth applications facilitate best-practice in diabetes and CVD service delivery and disease management in remote Indigenous Australian communities?’ The TEAMSnet study will provide evidence regarding the efficacy and cost-efficacy of telehealth facilitation in the management of diabetes, its complications and related conditions in remote and very remote Indigenous Australian communities. We anticipate benefits in the area of new and modified diabetes management strategies alongside improvements in patient self-management.

This multi-pronged telehealth approach may facilitate the management of diabetes, an increasingly prevalent and complex chronic condition and public health problem. The benefits of telehealth facilitation of retinal screening, lifestyle modification and electronic decision support might then be extended to other complications of diabetes and common co-morbidities.

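### The stated covariates cannot separate the intervention from calendar-time change in an uncontrolled within-person pre-post comparison, yet the article describes the result as efficacy

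*Protocol article*

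**What the plan says.** The design has one group. Under Study design the article states: "This is a pre-post study of technology-facilitated management of diabetes, CVD, and diabetic retinopathy". All three health services receive the intervention, and no control group, control site or external series is described. On timing: "Recruitment and intervention are anticipated to occur over a 3-year period".

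The comparison data are each participant's own history (Pre-study data): "Site partners will collaborate to audit the Communicare EHR for each participant in order to obtain the required pre-study data". The abstract gives the endpoint: "The primary outcome is increased participant adherence to clinical appointments, a marker of engagement and self-management".

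Under Data analysis, site differences are to be examined, and then: "Analysis of covariance (ANCOVA) will be used to compare differences between groups". The groups are not defined. The next sentence is the only one on confounding: "To assess confounding, covariates will include age, gender, and established and emerging risk factors for CVD, diabetes and diabetic retinopathy, as appropriate". A multilevel model is named, but only as a way of handling missing data. No term for calendar period or season appears, and the limitation is not acknowledged.

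The abstract's Background states the aim as investigating efficacy, and the Discussion says: "The TEAMSnet study will provide evidence regarding the efficacy and cost-efficacy of telehealth facilitation in the management of diabetes".

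**The concern.** When every participant contributes both a before and an after value, a characteristic that does not change between the two cannot confound the change. Gender, age at enrolment and baseline risk factors may predict who changes more, but they are balanced across the two periods by construction. What differs systematically between the periods, apart from the intervention, is time: staffing, service organisation, season and recording practice in the health record. Nothing in the stated adjustment addresses these. Site does not help either, because no site is untreated.

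At stake is the reading of the primary result. A background rise in attendance would look like benefit, and a background fall would hide one. A reader who sees a covariate-adjusted estimate may believe that confounding has been dealt with when its main source has not been touched.

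**Working it through.** **Inputs from the protocol article**
- 600 participants and 25% attrition (Sample Size): 600 × 0.75 = 450 completers.
- Alpha 0.05 (Data analysis). Sidedness is not stated; two-sided is taken, in line with the 95% confidence intervals.
- Target difference 15% (Sample Size), read here as percentage points.

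**Assumed, because the documents do not give them**
- Proportion of participants whose adherence status differs between periods (discordance): 50%, with 20% to 50% as the range.
- Background drift d between the two periods.
- Intervention effect: zero.

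**The plan's own figure.** The stated minimum of 490 cannot be confirmed, since no baseline rate or pairing is given. A near match needs two independent groups, a two-sided continuity-corrected test, an assumed baseline of about 35% to 50%, and attrition already included (for example 366 / 0.75 = 488). Nothing below depends on it.

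**Step 1: does the stated adjustment remove drift?** Write the within-person change as Δᵢ = α + β′(xᵢ − x̄) + eᵢ, where xᵢ holds pre-enrolment covariates. Because the covariates are centred, least squares gives α̂ = mean(Δ), which is the unadjusted change. A simulation with 450 pairs, adjusted for age, gender and one baseline risk factor, agrees:

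| Drift put in | Unadjusted estimate | Adjusted estimate | Significant |
|---|---|---|---|
| 0 | 0.0 points | 0.0 points | 5% |
| 5 points | 5.0 points | 5.0 points | 35% |
| 10 points | 9.9 points | 9.9 points | 88% |

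The adjustment removes none of the drift.

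**Step 2: how often would drift alone be significant?** For a paired binary outcome, SE = √(discordance / n) = √(0.5 / 450) = 0.0333, or 3.3 points. The rejection probability is Φ(d/SE − 1.96) + Φ(−d/SE − 1.96).
- d = 3 points: d/SE = 0.90, giving 0.147.
- d = 5 points: d/SE = 1.50, giving 0.323.
- d = 7.5 points: d/SE = 2.25, giving 0.614.

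**Step 3: sensitivity to the assumed discordance** (450 pairs, 50% down to 20%):
- No drift: 5%.
- 2 points: 9% to 16%.
- 5 points: 32% to 66%.
- 10 points: 85% to more than 99%.

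The 50% figure is therefore the mildest in this range. Five points is 5/15, one third of the target difference.

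**Step 4: the other direction.** The formula is symmetric in d. A true gain of 5 points with a background fall of 5 points gives an expected difference of 5 − 5 = 0.

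**The case against.** The strongest reply is that the confounding sentence may not be meant for the pre-post contrast. It follows a sentence on comparing undefined groups and comes after mentions of site differences and predictors of outcomes. For those analyses, age, gender and risk factors are ordinary covariates. The list is also open, since it applies as appropriate, and an analysis plan that is not shown could add calendar period. This stands in part: the documents do not establish that this set was chosen for the pre-post contrast. But it is the only confounding strategy stated, and both the uncontrolled design and the efficacy wording are fixed in the article itself.

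Three stronger readings are tempting and are not supported.
- A reader might infer that drift will be reported as efficacy and that the error rate is already above 5%. No background trend is given. Drift could be zero, upward or downward, and the percentages above rest on assumed drift and assumed discordance. They also come from a paired binary test, not the planned ANCOVA.
- A reader might infer that the plan adjusts for post-intervention blood pressure or metabolic control. The article does not say so. These are hypothesised outcomes (Background), which is a reason to exclude their later values explicitly, not evidence that they will be used.
- A reader might infer that the data for a full segmented time-series model are already held. The abstract mentions encounter history and the audit covers use of health services, but dates, look-back and resolution are not stated. Clients need only six months' registration (Exclusion criteria). Consent and baseline imaging take place at the same contact (Sample recruitment), so enrolment may itself depend on attendance, and person-time before enrolment comes only from people who later joined. The components also arrive in phases, at baseline, about 6 months and about 18 months, so a single step at enrolment would not match the rollout.

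It may also be said that this is a known limit of an openly declared pre-post design. That is true, but the article neither acknowledges the limit nor words its conclusion accordingly.

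**Conclusion.** The point holds in a conditional form. The comparison is uncontrolled and within-person over about 3 years, and the stated covariates cannot distinguish the intervention from calendar-time change. Any drift in attendance, in either direction, passes in full into the estimated effect. With 450 pairs, 50% discordance and no intervention effect, assumed drifts of 3, 5 and 7.5 points give significance in 15%, 32% and 61% of trials; lower discordance makes this worse. The actual drift is unknown, so these figures illustrate sensitivity and do not estimate the study's error rate. The plan should be corrected because the issue bears on how the primary conclusion is read. With 576 of 600 already recruited, adding a control group is impractical, and the analysis and the wording are the remaining levers.

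**What to change.** 1. **Data analysis:** add an analysis of the primary attendance outcome by calendar interval within participant. Use a mixed model with participant and site effects, calendar period and season, and an intervention-exposure term that reflects the phased components. Draw on the audited Communicare encounter history as far back as its dates permit, and report the result alongside the simple pre-post difference.
2. **Data analysis:** restrict adjustment covariates to values recorded before enrolment.
3. **Abstract and Discussion:** describe the result as a change associated with telehealth facilitation, not as efficacy.

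**Cost:** more analysis work and a wider confidence interval, but no additional participants. Whether the audit holds usable dates must be confirmed first. Pre-enrolment histories as short as six months, and enrolment at a clinic contact, limit how well the trend can be separated. Willingness to see a doctor at least twice is an entry condition, and calendar terms do not fully remove that selection. The wording change is therefore needed whichever model is fitted.

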Our second objective is to improve the timely exchange of relevant health information and the communication between a patient’s health care providers. CDMP facilitates this through use of a unique practitioner access code that enables a specialist medical practitioner, such as an optometrist or ophthalmologist, to view only relevant patient data, including reports.
*Improve engagement of patients in self-care, particularly adherence to clinical visits*
Our third objective is to improve engagement of patients in self-care. GRI retinal imaging will provide both a powerful education and retinopathy assessment opportunity. In addition, a third technology, (3) a custom-built e-mobile health device in the form of a tablet with viewable clinical data, GRI images and educational content, developed with clinical and Aboriginal Health Worker input, will facilitate health worker communication with patients between medical consultations and is aimed at improving relationships and engaging patients in self-care. A fourth application, (4) a suite of lifestyle surveys and a related reporting template based on CARPA recommendations for smoking, nutrition, alcohol, physical activity and emotional well-being [SNAPE] has been developed and is accessible via CDMP in a clinical setting or via the mobile tablet application anywhere. This is designed to be both a patient engagement and clinical management tool that facilitates the measurement, goal-setting and monitoring of important lifestyle risk factors for CVD, diabetes and diabetic retinopathy. All three telehealth reports, EDS, GRI and SNAPE, will be accessible via either the EHR [Communicare] or CDMP.

Apart from the development and implementation of the four technologies, the primary outcome includes improved adherence to clinical care, such as eyecare visits. Secondary outcomes include reduction in hospitalizations and cost-efficacy of the suite of technologies, both individually and collectively.

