### Data collection and outcome measures

Demographic data (including age, gender, postcode, contact details) and self-report measures are obtained from each participant at baseline and/or at the 6-month survey administration visit. Pre- and post-study clinical data such as blood and urine biochemistry, blood pressure and anthropometric measures including height and weight are also collected. Pre- and post-study health care resource utilization is captured through EHR records and includes information on hospitalizations and eye-care consultations.

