## Sample Size

For a conservative differential in adherence to subsequent care of 15%, and with 80% power, the minimum sample required is 490. Estimates are based on a 25% attrition rate. We will therefore need 600 participants across the three partner sites.

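### The missing-data rule makes no exception for the primary outcome, which is attendance, so treating people who stop attending as missing could bias the pre-post comparison in favour of the intervention

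*Protocol article*

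**What the plan says.** All references are to the protocol article.

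- **Outcome.** The abstract states: "The primary outcome is increased participant adherence to clinical appointments, a marker of engagement and self-management". Study aims and objectives says that "the primary outcome includes improved adherence to clinical care, such as eyecare visits".
- **Design.** Study design states: "This is a pre-post study of technology-facilitated management of diabetes, CVD, and diabetic retinopathy". No concurrent control group is described.
- **Sample size.** "For a conservative differential in adherence to subsequent care of 15%, and with 80% power, the minimum sample required is 490". The next sentence reads: "Estimates are based on a 25% attrition rate". The recruitment target is 600.
- **Missing data.** Data analysis states: "Complete case analysis and, where reasonable, multiple imputation will be employed for the management of missing data". It gives the sources: "Missing data may occur due to drop-out, missed assessments or item non-response". It then offers a full-likelihood multilevel model, which it says relies on missingness depending only on observed data, and names multiple imputation again.
- **Source of attendance data.** Data collection and outcome measures states: "Pre- and post-study health care resource utilization is captured through EHR records", and lists eye-care consultations among the items. Pre-study data describes an audit of the Communicare record for each participant.

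Nowhere does the article say whether a participant who stops attending counts as non-adherent or as missing.

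**The concern.** In most trials drop-out is a nuisance that runs alongside the outcome. Here the two overlap: someone who stops coming to the clinic has failed on the primary outcome and is also a likely drop-out. A complete-case analysis of attendance would then keep mainly those who attended. The listed alternatives do not clearly repair this. Imputation and the multilevel model both rest on missing at random, which is doubtful if the record is missing because the person stopped attending.

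A controlled trial might cancel part of such selection between arms. A single-group pre-post comparison cannot, and the selection acts on the post period only. The error therefore runs towards a rise in adherence, which is the result the study hopes to find. At stake is whether a reported rise reflects the telehealth package or the loss of people who disengaged.

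**Working it through.** **The plan's own figures.** The 490 cannot be reproduced from the stated inputs, because no baseline adherence is given. It can be approached by assumption. For two independent proportions of 50% and 65%, two-sided 0.05, 80% power and a continuity correction, 183 per group are needed. That is 366 in total, and 366/0.75 = 488. If 490 is instead the number before attrition, 490/0.75 = 654 and 490 × 1.25 = 613, neither of which is 600. What matters here is only that the 25% attrition is attached to the calculation for the adherence endpoint. With 600 enrolled, 150 would be lost and 450 would remain.

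**Inputs**
- a = 0.25, the fraction lost (Sample Size section).
- p = true adherence, the same before and after, so there is no effect. It is not given in the article; 45% and 50% are assumed.
- q = post-period adherence among those lost. It is not given; it is varied from 0 to p.
- r = within-person correlation of pre and post adherence. It is not given; it is varied from 0 to 1.
- The 15% differential is read as 15 percentage points.

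**Formula.** Completers' post rate is (p − a·q)/(1 − a). If loss depends on post-period adherence, the lost group's pre rate is p − r(p − q), and the completers' pre rate is p + r(p − q)·a/(1 − a). The apparent rise is therefore

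(1 − r)(p − q)·a/(1 − a) = (1 − r)(p − q)/3.

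Setting r = 0 also gives the rise when completers' post rate is set against the whole cohort's pre rate.

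**Results, in percentage points, with no true effect**

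| Situation | p = 45% | p = 50% |
|---|---|---|
| Loss unrelated to attendance (q = p) | 0 | 0 |
| All lost are non-adherent (q = 0), r = 0 | 15.0 | 16.7 |
| q = 0, r = 0.3 | 10.5 | 11.7 |
| q = 0, r = 0.5 | 7.5 | 8.3 |
| q = 0, r = 0.7 | 4.5 | 5.0 |
| Lost half as adherent (q = p/2), r = 0 | 7.5 | 8.3 |
| q = p/2, r = 0.5 | 3.8 | 4.2 |

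In people, at p = 50% and q = 0: 300 of 600 are adherent, all 300 are among the 450 retained, and 300/450 = 66.7%. The extreme case also moves with the baseline: p/3 is 10.0 points at 30% and 20.0 points at 60%.

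**Would a missing-at-random method remove it?** Take p = 50%, q = 0 and r = 0.5, and impute post adherence from pre adherence.
- Joint proportions (pre, post) are: yes-yes 0.375, yes-no 0.125, no-yes 0.125, no-no 0.375.
- Half of the post-period non-adherent are lost (0.25 of 0.50).
- Observed post adherence is 0.375/0.4375 = 85.7% in the previously adherent and 0.125/0.3125 = 40.0% in the others.
- Averaged over the whole cohort: 0.5 × 0.857 + 0.5 × 0.400 = 62.9%, against a true 50%.

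The spurious rise is 12.9 points. That is below the 16.7 of the unpaired complete-case comparison but above the 8.3 of the paired one.

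**If attendance is read from the record for everyone,** no one is lost from the outcome and this artefact is 0.

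**The case against.** The strongest reply is that the problem may never arise. Utilization in both periods is to come from the electronic record, and that record is to be audited for each participant. Someone who skips a study visit can still have attendance observed, and a missed study assessment is not the same thing as a missed clinical appointment. The listed sources of missing data may refer mainly to surveys, blood tests and measurements. This stands in part: the data needed to avoid the bias are already planned. But the missing-data rule is stated for the study as a whole with no exception for the primary outcome, and attrition is attached to the adherence calculation. If attendance were read from the record for all, dropping out of study visits alone would cost little on that endpoint.

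Three stronger readings are tempting, and the article does not support them.

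- A reader might infer that non-attenders are removed. No sentence says so.
- A reader might infer that the plan rests on complete-case analysis alone, or that missing at random certainly fails. Two further methods are listed, and audited prior attendance could inform them. Missing at random is doubtful here, not disproved.
- A reader might infer that adjustment for the lifestyle survey conditions on attendance a second time. Survey items are not named as covariates, and the surveys can also be completed outside the clinic by tablet.

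On scope, a condensed article may leave detail to an analysis plan not shown here. The point does not rest on an omitted detail: the article states a general rule, and that rule suits this outcome badly.

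**Conclusion.** The concern holds as a conditional one. As written, the rule permits an analysis that conditions the primary result on attendance, and nothing in the article prevents it. With 25% loss and an assumed baseline of 45–50%, the spurious rise in a complete-case analysis runs from 0, through about 4–12 points under intermediate assumptions, to about 15–17 points at the extreme. Only the extreme matches the 15-point differential. It needs every lost participant to be a non-attender and earlier adherence to be unrelated to loss, which is hard to credit if drop-out marks poor attendance. Attrition is undefined and may include death or relocation, which would pull the figure down. A reader should therefore not take about 15 points as the expected bias. Even the middle of the range is large relative to the target, and its direction favours the intervention.

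**What to change.** State a separate rule for the primary outcome:

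- The primary adherence analysis includes all consented participants.
- Attendance is taken from the Communicare record in both the pre and post periods, whether or not study visits were completed.
- A missed appointment counts as non-adherence, not as missing data.
- Follow-up ends only at death or documented transfer of care.
- Complete-case analysis is kept as a sensitivity analysis.
- Multiple imputation is used for clinical and survey variables only.

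The cost is analysis wording, since the record audit and the capture of post-study utilization are already planned. One practical check is needed: the article mentions consultations but does not say whether booked appointments that were missed are also extracted, so the extract should be confirmed to hold both. With 576 of 600 participants already recruited when the article was written, the rule should be fixed before outcome data are analysed.
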